#### Sleep quality and disturbances

The PSQI is a widely used self-reported measure of sleep quality in clinical populations. This scale consists of 24 questions to be rated, relating to the past month (0–3 for 20 items while 4 items are open-ended), 19 of which are self-reported and 5 of which require secondary feedback from a room or bed partner [22]. Only 19 items (15 rated 0–3 and 4 open-ended) are used for the evaluation of sleep quality as perceived by the patients. The open-ended items are also scored as categorical values (rated 0–3) as per the range of values reported by the patients. These 19 self-reported questions are then used to generate scores, which range from 0 (no difficulty) to 3 (severe difficulty), representing the PSQI’s seven components: subjective sleep quality, sleep latency, sleep duration, habitual sleep efficiency, sleep disturbances, use of sleep medications, and daytime disturbance. The total score is generated by the summation of the component scores, and can range from 0 to 21, with a higher score corresponding to a reduced sleep quality. A cutoff score of 5 or 8 represents a “poor” sleeper in the general population or in cancer patients, respectively. A change of 3 points or more on the PSQI is considered a minimal clinically important difference. Brackhaus et al. [23] showed the PSQI to have a high test–retest reliability and a good validity for patients with primary insomnia.

#### Sleepiness

The Epworth Sleepiness Scale (ESS) is a simple self-report scale used to assess daytime sleepiness. The scale asks the respondent to rate the probability of falling asleep in a variety of situations such as reading, watching TV, sitting inactive in public place, or while riding in a car, resting in the afternoon, talking to someone, sitting quietly after lunch, stopping in traffic. A 4-point rating scale is used ranging from 0 (no chance of dozing) to 3 (high chance of dozing). The scores are summed to determine a total ESS score, which ranges between 0 and 24. The higher the score, the higher the person’s level of daytime sleepiness. A cut-off value of 10 (ESS total score > 10) is usually considered to detect excessive daytime sleepiness that could be a sign of a sleep disorder or medical problem. The ESS has been widely used in a variety of studies with normal sleepers and sleep disorders patients.

#### Anxiety and depression

Patients complete the Hospital Anxiety and Depression Scale (HADS) [24]. This scale is a 14-item self-report instrument with 7 questions related to anxiety and 7 others to depressive symptoms. The answer format offers four response options, which are scored with values ranging from 0 to 3 (0 = not at all to 3 = nearly all the time). Thus, each subscale (depression and anxiety) yields a score values between 0 and 21. HADS defines three ranges for both scales: 0–7 (no symptoms), 8–10 (doubtful symptomatology), and 11–21 (some symptomatology). It is possible to calculate a HADS total score by summing the anxiety and depression items [25].

#### Circadian typology

Patients complete the Horne and Östberg Morningness-Eveningness Questionnaire (MEQ), which is widely used to determine diurnal preference [26]. The MEQ is a 19-item questionnaire. The total score gives 5 typologies: definite morning type (score 70–86), moderate morning type (score 59–69), intermediate (score 42–58), moderate evening type (score 31–41), definite evening type (score 16–30).

#### Dim light melatonin onset (DLMO)

The time of onset of melatonin secretion in light condition (< 50 lx), in the evening, called the dim light melatonin onset (DLMO) phase is assessed for each patient. Patients wear glasses composed of acrylic lenses and a UV-530 filter (Bio Optik, Lux Therapie, Strasbourg, France), filtering the blue component of light, 1 h before the beginning of the first sampling. Patients are prompted to give 5 to 6 saliva samples of 2 ml every 30 min using Salivettes (Sarstedt, Newton, NC) 4 h before their average bedtime. The participants tip the cotton swab from the Salivette into their mouths and roll the cotton swab in their mouths for up to 5 min until saturated, before spitting it back into the Salivette. Toothpaste or mouthwash are not allowed during the phase assessments. Small snacks and fluids are permitted, except in the 20 min before each sample, and participants are required to rinse and brush their teeth with water while remaining seated 10 min before each sample if they had consumed food or drink. Participants are not permitted to consume any alcohol or caffeine at least 24 h before each phase assessment.

After collection, saliva samples are frozen at -20 °C, then at -80 °C until analysis. Salivary melatonin is determined by a Direct Saliva Melatonin ELISA kit from NovoLytiX GmbH society (Witterswill, Switzerland). Saliva specimens from a given subject are run with the same assay kit [27, 28]. The method used is the relative threshold 2-SD, defined as 2 times the standard deviation of the mean of the 3 baseline values. The relative threshold method has been shown to have low intra-individual variability [29, 30].

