Moreover, exercise is recommended during treatment with curative intent. Aerobic and resistance exercise has been shown to reduce fatigue, preserve cardiorespiratory fitness and physical functioning, as well as improve quality of life and depression symptoms [14]. Several trials demonstrated that exercise interventions are feasible in early breast cancer patients and have a low risk of severe adverse events [15, 16].

However, few studies have explored the efficacy of an exercise program for cancer-related insomnia among patients undergoing breast cancer treatments. In this regard, we hypothesize that exercise programs can have a beneficial effect on insomnia for breast cancer patients.

We designed the present randomized FATSOMCAN trial, to examine, in non-metastatic early breast cancer patients with an insomnia diagnosis, the effect on sleep quantity of an individualized, intermittent aerobic exercise training regimen (45 min, 3 times a week), comprising both moderate and high intensity exercise, for a period of 3 months. Secondary objectives are to evaluate the effects of this supervised exercise program on other parameters such as sleep disorders, sleepiness, anxiety/depression, core body temperature and salivary melatonin rhythm. Furthermore, fatigue, pain, inflammatory and cardiorespiratory fitness variables, and level of physical activity (PA) are assessed.

We hypothesize that a supervised exercise program will reduce insomnia and improve the quality and quantity of sleep. Exercise will increase cardio-respiratory fitness, with an improvement in inflammatory variables. We suppose that these modifications will be accompanied by a reduction in sleepiness, anxiety/depression, fatigue and pain. Moreover, we hypothesize that patients who participate in the supervised exercise program will maintain these benefits at the three-month follow-up.

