**Fig. 2 Fig2:**
[figure not shown]
Representation of treatment schedule and different times of evaluation and questionnaire completion

At T-1, all potentially eligible patients have a clinical interview according to the DSM-5 to diagnose the presence of insomnia before treatment by chemotherapy. They also complete the study questionnaires [i.e., the Insomnia Severity Index (ISI), the Pittsburgh Sleep Quality Index (PSQI), the Epworth Sleepiness Scale (ESS) and Hospital Anxiety and Depression Scale (HADS)] and a sleep diary for 2 weeks. The interview, questionnaires and sleep diary constitute the baseline values before inclusion. A clinical examination, including medical history, use of analgesics (type, level, dose), lifestyle habits (work, family environment, physical activity, smoking, alcohol), is also carried out.

At T0, one week after completion of the first sequence of the chemotherapy, patients have a clinical interview, complete the questionnaires and sleep diary again. If insomnia is confirmed, patients can then be included.

At T1, at the end of the 3-month exercise intervention (T3) and at 6 months (T6) of the follow up period, objective sleep parameters, salivary melatonin and core body temperature rhythm are evaluated. At T1 and T3, fatigue, pain, inflammatory variables and cardiorespiratory fitness are assessed. At T3, DMS-5 interview, questionnaires and sleep diary are completed again. From T1 to T6, the level of PA is followed (Fig. 2).

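### The melatonin-onset threshold is written as 2 SD of the three baseline values without adding their mean, so it can lie below the patient's own baseline

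*Protocol article*

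**What the plan says.** The Background of the Protocol article lists, among the secondary objectives, effects on "sleepiness, anxiety/depression, core body temperature and salivary melatonin rhythm". The text with Fig. 2 says that at T1, T3 and T6 "objective sleep parameters, salivary melatonin and core body temperature rhythm are evaluated".

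The section on dim light melatonin onset gives the threshold: "The method used is the relative threshold 2-SD, defined as 2 times the standard deviation of the mean of the 3 baseline values". It supports the choice with the statement "The relative threshold method has been shown to have low intra-individual variability".

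The same section sets the sampling: "Patients are prompted to give 5 to 6 saliva samples of 2 ml every 30 min", timed "4 h before their average bedtime". It does not say which samples are the three baseline ones. No other section restates the threshold or adds a baseline mean to it.

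**The concern.** An onset threshold has to sit above the patient's pre-onset level, so that crossing it marks a rise. A multiple of the SD alone measures scatter, not level. A patient with a steady baseline has a small SD and so a very low cut-off, and the steadier the baseline, the lower the cut-off falls relative to it. Flat samples would then be read as onset.

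If the sentence were applied as written, the recorded DLMO would for many patients reflect when sampling began, or the first sample after baseline, and not when melatonin rose. A real shift in rhythm between groups would be blurred or hidden.

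**Working it through.** The article states no figure that depends on the DLMO rule, so there is nothing to reproduce. The check has four steps.

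**1. Algebra.** Let m and s be the mean and SD of the three baseline values. The literal threshold is 2s. It lies below m when 2s < m, that is, when s/m < 0.5: an observed CV under 50%.

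- Baselines 1.0, 1.2, 1.4: m = 1.2, s = 0.2. Literal threshold 2 × 0.2 = 0.4, below all three values. Mean plus 2 SD = 1.2 + 0.4 = 1.6.
- Baselines 0.5, 1.5, 2.5: m = 1.5, s = 1.0 (CV 67%). Literal threshold 2.0, above the mean but still below the third baseline value. Mean plus 2 SD = 3.5.

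The phrase could also be taken to mean the standard error, s/√3. That gives 2 × 0.2/1.732 = 0.23 in the first example, which is lower still.

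**2. How often a sample at baseline level exceeds the literal 2s.** Simulation, 400,000 draws per setting. Baseline is flat with mean 1, and values are normal (negatives set to zero) or lognormal. The underlying CV is assumed.

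| Assumed CV | First sample above 2s (normal / lognormal) | Flat fourth sample above 2s (normal / lognormal) |
|---|---|---|
| 0.2 | 97% / 98% | 99% / 99% |
| 0.3 | 87% / 89% | 87% / 88% |
| 0.5 | 63% / 70% | 59% / 62% |
| 0.8 | 40% / 55% | 39% / 44% |
| 1.0 | 32% / 48% | 34% / 38% |

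Under the standard-error reading, the first sample exceeds the threshold in 53–100% over CVs of 0.1 to 1.5.

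**3. The same check with mean plus 2 SD.** With n = 3, the largest possible value of (x − m)/s is (n − 1)/√n = 2/√3 = 1.155. This is below 2, so no baseline sample can cross at any CV.

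A fourth sample with no rise can still cross, because three values estimate the SD poorly. For normal data, (x₄ − m)/(s√(4/3)) follows a t distribution with 2 degrees of freedom. The crossing probability is P(t₂ > 2/1.155) = P(t₂ > 1.732) = 0.5 − 1.732/(2√5) = 0.113. Across both distributions and all CVs simulated, it is about 11–18%.

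**4. Sampling clock.** If the first sample is taken 4 h before bedtime, sample k falls at −4 + 0.5(k − 1) h. The fifth is at −2 h and the sixth at −1.5 h. An onset later than that cannot be observed. If the first three samples are the baseline, two or three remain in which to see a crossing.

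**The case against.** The strongest reply is that this is a slip of language. The article calls the method a relative threshold, mentions the mean of the baseline values, and cites sources for it. A relative threshold that ignores the baseline level makes little sense, so the laboratory may well apply mean plus 2 SD. That is probably right, but it does not dispose of the point. The sentence is the only operational definition in the article, and it gives a different number from the one presumably meant.

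A second reply is that if the first three samples are reserved as baseline, the first cannot be declared the onset. That is fair, and the article does not settle it. The fourth-sample column above shows that the problem then moves to the first eligible sample.

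A reader might go further and infer any of the following, which the documents do not support:

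- *Most patients will be given an onset at the first sample, so the endpoint cannot show an effect.* This needs the literal rule to be applied and a CV below about 0.6 (normal) or 0.9 (lognormal). The article gives no CV.
- *A known share of onsets is missed because sampling stops early.* The share depends on an assumed onset time. With an SD of 1 h and a mean onset 3 h before bedtime, 16% fall after the last of 5 samples and 7% after the last of 6. At 2 h the figures are 50% and 31%; at 1 h, 84% and 69%. Onsets before or during the baseline samples are a separate loss that later sampling would not recover.
- *The article omits interpolation and censoring rules.* Such detail may stand in the full protocol or analysis plan.

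**Conclusion.** The threshold is wrong as written and should be corrected. That it falls below the baseline mean when the observed CV is under 50% is algebra and needs no outside figure. How many patients would be affected is conditional on the literal rule being used and on the baseline CV: a large majority for steady baselines (CV 20–30%), and about half or fewer at CVs of 0.8–1.0.

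The sampling limit is a secondary note. It follows from the stated schedule if the first sample is at −4 h, but its size cannot be derived from the article.

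The reach is limited. Melatonin rhythm is a secondary objective in the Background and is not named in the short list that opens the Secondary endpoints section. The TST primary endpoint, the 57 evaluable and 64 randomized patients, and the interim analyses do not depend on it.

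**What to change.** State the threshold as the mean of the three baseline concentrations plus 2 of their SDs, and say which samples form the baseline. If this is what the laboratory already does, confirm it. Apply the rule uniformly to the stored assay results from T1, T3 and T6. This is a change of wording, with no new samples or visits. Note in the report that three baseline values make the SD imprecise, so a flat fourth sample still crosses in about 11–18% of cases.

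For the sampling limit, report by group and visit how many patients show no crossing. Treat them as right-censored at their own last sample time (−2 h or −1.5 h if sampling starts at −4 h) and do not drop them. This costs some programming. The sampling schedule itself should stay as it is: data collection began in February 2021, and a change now would add a procedure and mix windows across patients and visits.

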#### Core body temperature rhythm

Circadian core body temperature (CBT) rhythm is established as a major influence on the sleep/wake cycle. CBT is measured using four iButtons (Humeau Laboratories, France) placed at each wrist and infraclavicular fossa, secured with a Comfell protective film. Recording begins in the middle of the afternoon and continues for 48 h with an acquisition frequency of one measurement every 10 min. Data collection is obtained from the Thermotrack software (ref: 303.000105.47) [31].

The analysis of the circadian rhythm of CBT [acrophase (h:min), batyphase (h:min), period (h) and mesor (°C), amplitude (°C)] are carried out by a Cosinor technique (Time Series Analysis Seriel Cosinor, Version 6.3, Soft Technology Expert, Laboratory of Applied Statistics and BioMedical Computing, Richelieu, France). Acrophase and batypase are the measures of the time of overall high and low values recurring in each cycle. Period represents the duration of one cycle, MESOR (Midline Estimating Statistic Of Rhythm), is a rhythm-adjusted mean, and amplitude is a measure of half the extent of predictable variation within a cycle.

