## Abbreviations

BPI-SF: Brief pain inventory short form
CBT: Core body temperature
CBT-I: Cognitive behavioral therapy for insomnia
CG: Control group
CRP: C-reactive protein
DSM-5: Diagnostic and statistical manual of mental disorders
ECG: Electrocardiogram
EEG: electroencephalogram
ESS: Epworth sleepiness Scale
GET: graded exercise test
HADS: Hospital Anxiety Depression Scale
HR: Heart rate, IL-6:interleukin 6
TNF-alpha: tumor necrosis factor alpha
ISI: Insomnia severity index
IT: Interval training
ITT: Intention-to-treat
MEQ: Morningness-eveningness Questionnaire
MFI-20: Multidimensional fatigue inventory 20
mITT: Modified intention-to-treat
MTB: Multidisciplinary tumor board
PaCO_2_: Partial pressure of carbon dioxide in arterial blood
PaO_2_: Partial pressure of oxygen in arterial blood
V˙O_2_ Peak: Peak oxygen uptake
pH: Hydrogen potential
PSG: Polysomnography
PSQI: Pittsburgh Sleep Quality Index
REM: Rapid eye movement
RPE: Rating of Perceived Exertion
SaO_2_: Arterial oxygen saturation
SD: Standard deviation
SE: Sleep efficiency
SOL: Sleep onset latency
SpO_2_: Peripheral capillary oxygen saturation
TG: Training group
TIB: Time in bed
TST: Total sleep time
TTN1: Total time in stage 1 sleep
TTN2: total time in stage 2 sleep
TTN3: total time in stage 3 sleep
TTREM: Total time in rapid-eye movement sleep
V˙CO2: Carbon dioxide flow
V˙CO2/V˙O2: Respiratory exchange ratio
V˙E: Ventilation minute
V˙E⁄V˙CO2: Respiratory equivalents in carbon dioxide
V˙E⁄V˙O2: Respiratory equivalent in oxygen
V˙O2: Oxygen consumption
VT1 and VT2: Ventilatory thresholds 1 and 2
WASO: Wake after sleep onset

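### Core body temperature rhythm is recorded only with skin sensors, so the level and amplitude reported as core values are skin temperature values

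*Protocol article*

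**What the plan says.** The Background of the protocol article lists the secondary objectives, which include effects on "sleep disorders, sleepiness, anxiety/depression, core body temperature and salivary melatonin rhythm". The text with Fig. 2 under Study outcomes schedules the measurement: at T1, T3 and T6, "objective sleep parameters, salivary melatonin and core body temperature rhythm are evaluated". The Abbreviations section fixes the meaning of the term: "CBT: Core body temperature".

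The method is in the section Core body temperature rhythm: "CBT is measured using four iButtons (Humeau Laboratories, France) placed at each wrist and infraclavicular fossa". The sensors are "secured with a Comfell protective film", and recording "continues for 48 h with an acquisition frequency of one measurement every 10 min". The output is then described in these words (the quotation stops just before the closing brackets): "The analysis of the circadian rhythm of CBT [acrophase (h:min), batyphase (h:min), period (h) and mesor (°C), amplitude (°C". A cosinor program produces these parameters.

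The section headed Secondary endpoints does not name temperature.

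**The concern.** The objective and the measurement do not refer to the same quantity. The objective concerns core temperature, while the instrument is four sensors on skin, two distal (wrists) and two proximal (below the collarbones). The text does not call the skin signal a stand-in for core temperature. It says core temperature is what the sensors measure, and it gives a level and an amplitude in °C under that name.

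Followed literally, a between-group difference in mesor or amplitude would be published as an effect of exercise on core temperature, although it could arise wholly at the skin. The article itself supplies reasons to keep the two apart. The Background names hot flashes among the causes of insomnia in these patients. Patients also wear an activity watch by day (Follow-up of physical activity) and an actimeter on the non-dominant wrist at night (Objective sleep parameters), while both wrists carry a temperature sensor. If these recordings overlap, a wrist reading could be affected by what covers the wrist.

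**Working it through.** The article gives no figure on this point that could be reproduced. The check is a comparison of every place where temperature appears.

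1. **Target quantity.** Background and Study outcomes: core body temperature and its rhythm. Abbreviations: CBT means core body temperature.
2. **Sensor sites.** Core body temperature rhythm section: 2 wrists + 2 infraclavicular fossae = 4 sensors, all held on the surface by film. Sensors at a core site: 0 of 4.
3. **Bridge from skin to core.** I looked for a conversion formula, a core-site calibration, or a statement that skin temperature is used as a proxy. None is given. The one reference in that section is attached to the sentence on data collection with the software, not to a statement that these sites measure core temperature.
4. **Amount of data.** 48 h × 6 readings per hour = 288 readings per sensor, and 4 × 288 = 1,152 per patient and visit. All 1,152 are surface readings. A dense series gives a precise skin rhythm but does not change what is measured.
5. **Each reported parameter in turn.**
   - Mesor (°C) is the rhythm-adjusted mean of the recorded series. The series is skin temperature, so this is a skin mean.
   - Amplitude (°C) is half the predictable variation of the recorded series, and so is a skin amplitude.
   - Acrophase and batyphase are the times of the high and low values of the skin series. They may carry information on circadian phase, but they are core times only if a known relation links the two rhythms, and none is stated.
   - Period is the cycle length of the skin series. As with the other timing parameters, its link to the core rhythm is indirect.
6. **Combination of sites.** The section lists the types of cosinor output. It does not say whether the sensors are averaged, fitted one by one, or fitted in pairs.

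Steps 2, 3 and 5 carry the point. Step 6 bears only on how the fix should be worded.

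**The case against.** The strongest reply is that this is loose wording with little consequence. The interest is in the rhythm, skin sensors may mark circadian phase indirectly, and phase is also measured separately by the dim light melatonin onset. The cited reference cannot be seen and may support the sensor method. Temperature is absent from the list under Secondary endpoints, and the primary endpoint, total sleep time, is untouched.

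Much of this stands. It limits the point to one secondary objective and protects the timing parameters as indirect markers. It does not rescue mesor and amplitude, which are absolute values in °C reported under the wrong name. Nor is this a detail that a condensed article leaves out, because the article states positively that core temperature is what these sensors measure.

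A reader might infer two stronger things that the document does not support:

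- **That the trial cannot address this objective at all.** Too strong: the recordings describe a skin temperature rhythm and may inform on phase.
- **That wrist and infraclavicular readings are averaged, which blunts the amplitude.** The article does not say so. Averaging two 24-h rhythms of equal amplitude with a phase difference d multiplies the amplitude by cos(d/2): 4 h (60°) gives cos 30° = 0.87, 8 h (120°) gives cos 60° = 0.50, and 12 h (180°) gives cos 90° = 0. These results need pooling, equal amplitudes and a given phase gap, and none of the three is in the document. They show what could happen if the sites were pooled, not what the plan does.

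**Conclusion.** The point holds as an error of labelling on a stated secondary objective. With 0 of 4 sensors at a core site and no conversion or proxy statement, the mesor and amplitude are skin temperature values at all three assessments, and the timing parameters are at most indirect for core phase. The conclusion rests on reading the film-held sensors as skin sensors, which the description of the sites supports, and on the full protocol not containing a conversion that the article omits.

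The size of any resulting bias cannot be given, because the article supplies no temperature amplitudes or phases for either site. The primary endpoint and the sample size are unaffected. This should be corrected before analysis, but it does not threaten the trial's main result.

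**What to change.** - In the Background objectives, the Study outcomes text and the Core body temperature rhythm section, rename the endpoint skin temperature rhythm, with the wrists as the distal site and the infraclavicular fossae as the proximal site. Align the abbreviation.
- Fit the cosinor separately for the wrist pair and for the infraclavicular pair, and say so. The distal-minus-proximal difference may be added. Making it the main summary would be a choice of method, not a requirement.
- Draw no direct conclusion on core temperature level or amplitude, and describe acrophase and batyphase as indirect for core phase.
- If the full protocol does hold a validated conversion to core temperature, state it in the method section.

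Cost: the same sensors and recordings serve, with no added procedure for patients. If one fit per patient and visit was planned, the extra work is one fit per patient and visit, at most 64 randomized patients × 3 assessments = 192 fits. The real price is a more modest claim, about skin rather than core temperature.
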